# Study Endpoints/Events/Outcomes

- 1. Primary Endpoint/Event/Outcome: Exercise minutes per week as assessed by an accelerometer for one week at baseline, 6 weeks, and 12 weeks.
  2. Secondary Endpoint(s)/Event(s)/Outcome(s): Self-reported weight and height; psychosocial variables assessed via a questionnaire including social support for exercise, self-efficacy, enjoyment, and outcome expectancies.

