# Procedures Involved

- 1. Study Design: Low active adults will be randomly assigned to either a 12-week home-based high intensity interval training exercise intervention or a wait-list control condition to examine the effect of the intervention on exercise minutes per week.
  2. Study Procedures:

Step 1: Telephone Screening, Consent, and Baseline Questionnaires: In response to an advertisement, potential participants will call, email, or text a study line, at which time they will complete a telephone screening interview with the Research Assistant (RA) to determine eligibility for the study. Participants who are eligible will be given detailed information about the study and the consent form will be reviewed. The RA will schedule a randomization appointment in two weeks. Participants will be told that they may need to cancel the appointment if the online consent and questionnaires are not completed.

1. Complete telephone screening
   1. If not eligible, end interview and thank them for their time
   2. If eligible:
      1. Schedule randomization appointment for 2 weeks
      2. Email link to consent form and questionnaires
      3. Explain ActiGraph procedures. The actigraph is a small device that is attached to the participant’s clothing/belt at the waist and measures physical activity amount and intensity. The actigraph functions as a method of measuring physical activity with the purpose of obtaining objective measurement of the participants’ physical activity.

Step 2: Send ActiGraph: Upon completion of the online consent form and questionnaires, send the ActiGraph with instructions and return envelope.

Step 3: Check on consent and questionnaires

1. If the ActiGraph is not received by the randomization appointment, the participant is to be called to cancel the appointment. The participant should be told that they will be called to reschedule the appointment once the ActiGraph is received.
   1. Once the ActiGraph is received, call the participant to schedule a time or if time permits, complete the randomization appointment at the time of the initial call.
   2. If the ActiGraph has been received, proceed with the scheduled randomization appointment.

Step 4: Baseline Session

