1. Participants are randomly assigned to either the exercise or wait-list control condition. The wait-list control condition will have the option of receiving the exercise intervention after the 12 weeks. The exercise intervention will be delivered via phone. Enter randomization date in REDcap.
2. Script: “The next thing we are going to do is to find out which of the two groups you have been randomly assigned to. This is completely random and unfortunately I have no control over which group you are assigned to. Let me access my form here to determine which program you are in.”
3. Exercise: “You have been randomly assigned to the exercise program. This program is designed to help you increase your exercise. I will work with you to make a plan on how you are going to fit exercise into your day. Do you have any questions before we start?”
4. Wait-List Control: “You have been randomly assigned to the wait-list control condition. This means that you will be contacted again in 12 weeks to complete your assessment. After your assessment, you will complete the exercise program if you would like to.”

Step 5: Intervention Sessions

- 1. The participant will be told when exercise should be stopped for safety reasons in order to minimize risk to the participant. See the intervention protocol (a supporting document) for more information. The intervention sessions will be audiotaped for quality control purposes.

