# Statistical Considerations

- 1. Data Analysis Plan: Between groups ANOVA tests will be used to determine if there are significant differences between the two groups on exercise minutes per week, weight, and the psychosocial variables.
  2. Power Analysis: This is considered a pilot study and therefore, a power analysis has not been completed.
  3. Statistical Analysis: See 15.1 above.
  4. Data Integrity: When completing the online questionnaires, participants will be prompted if they miss an item. They will not be allowed to submit their questionnaire until they have completed all items. The research assistant will also look over the ActiGraph data to make sure it has been worn each day and exclude any days it appears it has not been worn.

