# Multi-Site Research: N/A

# Resources Available

- 1. Resources Available: Based on the number of potential participants that are advertisements will reach, we believe that our recruitment target is feasible. We anticipate completing the entire research project in 6-9 months. The research activities are conducted out of an office that houses 2-3 research assistants, which have access to email and phones needed for the study. The computers are equipped with software that allows for downloading and analyzing the ActiGraph data. The PI is a licensed psychologist and therefore, if there are any psychological resources needed, she will provide these resources. All research assistants will be adequately trained on the research protocol. The research coordinator for this project has conducted several randomized trials and is familiar with the procedures involved in this type of project. She will oversee the research assistants on this projects to ensure that the protocol described in this application is adhered to. Additionally, as mentioned above, the exercise counseling sessions will be audiotaped. Ten percent of the audiotapes will be listened to by the PI on this study to ensure that fidelity to the treatment protocol is maintained. If the study protocol is not followed, the research assistants will be re-trained on the study procedures and the next five sessions will be audiotaped and listened to. This procedure will continue until the protocol is being followed. If the research assistant is not able to adhere to the protocol, they will be terminated.

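### Section 15.4 lets research assistants, who seem also to deliver the counseling, drop accelerometer days that look unworn, with no objective criterion and no masking to arm

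*Protocol*

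**What the plan says.** The primary outcome in Section 3 is "Exercise minutes per week as assessed by an accelerometer for one week at baseline, 6 weeks, and 12 weeks". Section 15.4 (Data Integrity) states who cleans these data and by what standard: "The research assistant will also look over the ActiGraph data to make sure it has been worn each day", and the assistant is then to "exclude any days it appears it has not been worn". It gives no zero-count rule, minimum daily wear time or second reading.

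Three other places bear on who that person is:

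- Section 5, Step 1, on telephone screening: "The RA will schedule a randomization appointment in two weeks".
- Section 5, Step 4, the script for the randomization call. The caller says "Let me access my form here to determine which program you are in" and, to those in the exercise arm, "I will work with you to make a plan on how you are going to fit exercise into your day". The caller's role is not named.
- Section 23 on staffing: "The research activities are conducted out of an office that houses 2-3 research assistants". The same section has the principal investigator listen to a tenth of the counseling recordings. If the protocol is not being followed, "the research assistants will be re-trained on the study procedures and the next five sessions will be audiotaped and listened to".

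Section 16 stores ActiGraph files under the study ID only. Section 17 keeps the original data file unaltered.

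**The concern.** The accelerometer is the trial's only objective measure; weight is self-reported and the remaining secondary outcomes come from questionnaires. Its value depends on its being processed in the same way in both arms. A rule that rests on how a day looks can be applied differently from one participant to the next. If the person applying it knows who received counseling, the difference can follow arm. With one week of wear per time point, each day is a seventh of the planned record, so a few discretionary exclusions can move a participant's figure. A difference between arms could then partly reflect the cleaning of the data, and a reader of the results could not tell.

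**Working it through.** The protocol gives no figure for this point, so there is nothing to reproduce. The check has two parts.

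**Who reviews, and what they may know.** Section 15.4 names the research assistant as reviewer. Section 23 responds to poor fidelity in counseling sessions by retraining research assistants and taping their next sessions, which makes sense only if research assistants counsel. The Step 4 script has one speaker both announce the arm and offer to plan the participant's exercise. Section 17 gives the downloading of ActiGraph data to a research associate. That does not clearly separate the roles: consent review during telephone screening belongs to the research assistant in Section 5 and to the research associate in Section 20, so the two titles appear interchangeable. No section masks the wear reviewer or gives the review to independent staff.

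On timing, Section 5 requires the baseline device to be back before the randomization appointment proceeds. The exposure is therefore mainly at the wear periods after randomization, although the protocol does not say when the review takes place.

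**What an exclusion does to the outcome.** The protocol does not say whether minutes are summed over retained days or averaged and rescaled to seven days. Start from 90 min/week, the eligibility ceiling in Section 8, and try both:

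| Days removed | Averaged over retained days × 7 | Summed over retained days |
| --- | --- | --- |
| None | 90 | 90 |
| One zero-minute day | 90/6 × 7 = 105 (+16.7%) | 90 (no change) |
| Two zero-minute days | 90/5 × 7 = 126 (+40%) | 90 (no change) |
| One day, minutes spread evenly | (90 × 6/7)/6 × 7 = 90 (no change) | 90 × 6/7 = 77.1 (−14.3%) |

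The same act of deletion can raise, lower or leave the weekly figure, depending on a derivation rule that is not given and on which day is removed.

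**Illustration of the effect on the test.** Assumptions, none of them in the documents:

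- 25 per arm (Section 10 gives 50 to be consented, with no allocation ratio);
- SD 45 to 90 min, mean 90 min, no true effect, two-sided 5% level;
- the averaging rule;
- one zero-minute day removed in a fraction *f* of one arm and none in the other.

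The bias is b = 15 × *f*. The standard error is SD × √(2/25), that is 12.7 to 25.5. The rejection rate is 1 − Φ(1.96 − b/SE) + Φ(−1.96 − b/SE).

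- *f* = 1/3: b = 5.0, rejection 5.4% to 6.8%
- *f* = 1/2: b = 7.5, rejection 6.0% to 9.1%
- *f* = 1: b = 15.0, rejection 9.1% to 21.8%

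Under the summing rule, the same deletions leave the rate at 5%.

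**The case against.** The strongest reply is that wear-time algorithms and valid-day definitions usually belong in a SAP, which is not shown, and that Section 15.4 is only a short quality check. Looking over the data does not exclude reading software output, and Section 23 says that the computers carry software for analyzing it. Files hold only the study ID, the original file is kept so exclusions could be redone, and this is a self-described pilot.

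Part of this stands. The retained original makes the harm reversible, and the absence of an algorithm would not by itself be a finding. But Section 15.4 does more than stay silent: it fixes appearance as the standard and names who applies it. A SAP with an algorithm would conflict with it unless it were amended. Study-ID files are a confidentiality measure and are not described as masking. In a team of 2-3 that also screens and seems to counsel these participants, an ID may not hide the arm. Nothing requires exclusions to be redone from the original file.

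A reader might infer more than the documents support:

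- **That the reviewer is known to be unblinded, or that research assistants assign participants.** Unblinding is inferred from roles and from the absence of masking. An unnamed caller reads the assignment from a form, and who generates the allocation is not stated. Nothing says that the person checking a file counseled that participant.
- **That a sedentary day will be mistaken for an unworn one.** The documents do not show this. A worn day with no exercise minutes would still be expected to record lighter movement.
- **That the exercise arm gains about 15 min/week.** That figure needs the averaging rule and a misjudged zero-minute day in every participant of one arm and in none of the other. The protocol supports neither condition.

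**Conclusion.** The point holds as a badly fixed rule. Section 15.4 lets subjective and potentially unblinded judgement edit the primary outcome, mainly after randomization, and the safeguards elsewhere in the protocol do not prevent this if the plan is followed as written.

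Neither the size nor the direction of any bias can be derived from the documents. The move from 90 to 105 min/week shows only the leverage of one deleted day under an averaging rule; under a sum the effect is nil or downward. The rejection rates rest on an assumed SD, allocation and pattern of exclusions, and should not be quoted as an estimate for this trial. That research assistants counsel is a reasonable reading of Sections 5 and 23, not an explicit statement. The change is worth making because it is cheap and protects the outcome on which the trial's conclusion rests.

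**What to change.** In Section 15.4, replace the judgement of appearance with a pre-set automated criterion for non-wear and for minimum daily wear time. Run it in the existing ActiGraph software with identical settings for both arms and all time points, and lock the valid-day flags before assignment is merged.

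Allow no manual overrides. In a team this small, a masked person to make them may not exist. If overrides are kept, log each with its reason, report exclusions by arm, and add a sensitivity analysis without overrides.

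The cost is a short amendment to Section 15.4 and a little processing work; Section 23 indicates that the software is already in place. The criterion will sometimes misclassify a day, but such errors would not depend on what staff know about arm.

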# Confidentiality

- 1. Data Security: As dictated by the study protocol, participants will complete questionnaires online. Information obtained from these questionnaires will be housed on a highly secured server, which will include a firewall, password protection, and several other precautionary mechanisms. Identifying information will not be included with the questionnaires. Participants will be assigned a study ID upon entering the study and only the study identification number will be included with the questionnaires. All data we collect will remain confidential. The information that matches the participant’s name with the participant’s study identification number, telephone numbers, and mailing addresses will be kept in a separate file from the questionnaire data. The ActiGraph data will be stored in files that include the participant’s study ID only.

# Provisions to Monitor the Data to Ensure the Safety of Participants

- 1. Data Integrity Monitoring. This study is considered a minimal risk study and therefore, will not include a data safety monitor or data safety monitoring board. However, there will be several steps taken to ensure the integrity of the data. Specifically, in order to gain access to the study data, the computerized data entry system will require a login and password. We will apply range rules and validation to the actual entry fields, where appropriate. Since the questionnaires are online, the data will be available directly to the research associate. The research associate will also be responsible for downloading the ActiGraph data. The research associate will make the data available to the Principal Investigator and other staff associated with the project once the study is completed, and all data have been collected, entered, and passed the audit procedures. The Principal Investigator will be the only person who can give permission for release of the aggregated data. Confidential information will not be released without the express written consent of the study participants. The original data file will stay in its original state.
  2. Data Safety Monitoring. All adverse events will be promptly reported to the IRB. In the proposal, one potential adverse event is injury due to participation in exercise. Participants will be instructed to call their healthcare provider and the exercise counselor for the current study if an injury were to occur. Additionally, to be proactive, participants will be asked during the telephone session if they have experienced any injuries.

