# Risks to Participants

- 1. Foreseeable Risks: There are two risks associated with this study. First, it is possible that a participant would experience a cardiac arrest or some other medical event as a result of exercise. This risk is considered minimal. To address this risk, participants will be given safety instructions that state when they should stop exercising and seek medical help. The second risk is the participant could sustain an injury while exercising. This risk is also considered minimal and participants will be given only exercises that are safe for them. Additionally, to minimize the risk of injury associated with exercise, participants will be screened for orthopedic problems and other medical issues that may make exercise unsafe or unwise. Participants will be advised to use/wear appropriate gear for their chosen form of exercise. If an injury or change in medical status occurs during the study, the intervention will be withdrawn until the participant obtains written clearance from their healthcare provider to continue to engage in exercise.
  2. Reproduction Risks: N/A.
  3. Risks to Others: N/A.

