# Provisions to Protect the Privacy Interests of Participants

- 1. Protecting Privacy: Data on individual participants will not be released. The data will only be presented in aggregate form and participants’ identifying information will not be shared outside of the research personnel who need to have direct contact with the participants.
  2. Access to Participants*:* N/A. This study does not involve accessing medical records.

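### The first named risk is a cardiac or other medical event, but both stated ways for the study to learn of an event are worded for injuries only

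*Protocol*

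**What the plan says.** Protocol section 13.0 (Risks to Participants, item 1) lists two foreseeable risks. The first is that "it is possible that a participant would experience a cardiac arrest or some other medical event as a result of exercise". The second is an exercise injury. Both are called minimal. Against the first risk the section states that "participants will be given safety instructions that state when they should stop exercising and seek medical help". It then sets a safety action with two triggers: "If an injury or change in medical status occurs during the study, the intervention will be withdrawn", and exercise resumes only after written clearance from the participant's healthcare provider.

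Section 17.0 (item 2, Data Safety Monitoring) states the reporting duty broadly: "All adverse events will be promptly reported to the IRB". It gives injury as one example of an adverse event, then states how the study hears of events. There are two routes:

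- the participant's own report: "Participants will be instructed to call their healthcare provider and the exercise counselor for the current study if an injury were to occur";
- a question from the counselor: "participants will be asked during the telephone session if they have experienced any injuries".

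Section 5.0 (Step 5) says participants will be told when to stop exercising for safety reasons and refers elsewhere for detail: "See the intervention protocol (a supporting document) for more information". That document is not shown.

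**The concern.** The duty to act covers injuries and medical events, while the stated means of finding out cover injuries alone. The less well covered risk is the graver of the two. A participant who has chest pain during a session, stops as instructed and recovers has not been injured, and can honestly say so when asked. The same holds for someone with a new diagnosis or a new pregnancy, although section 8.0 excludes angina symptoms, diabetes and current or planned pregnancy at entry.

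If the event is not volunteered, the clearance step in section 13.0 is not reached. The participant may then go on to the next session, at 70-85% of maximum heart rate (Study Summary), without the check the protocol itself calls for, and the IRB receives no report. Adverse-event counts for the pilot would also lean towards injuries because of how they were asked for.

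**Working it through.** The plan gives no figure to reproduce. The check is a comparison of text, followed by simple arithmetic on contact spacing.

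**Stated routes for each trigger**

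| | Injury | Medical event or change in medical status |
| --- | --- | --- |
| Named as a risk (13.0) | yes, second | yes, first |
| Triggers the pause (13.0) | yes | yes |
| IRB report due (17.0) | yes | yes, as an adverse event |
| Participant told to inform the study (17.0) | yes | not stated |
| Asked about on calls (17.0) | yes | not stated |
| **Stated detection routes** | **2** | **0** |

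**Other places that could supply a route**

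- Sections 5.0 and 13.0: participants are told when to stop and when to get medical help, but not to tell the study.
- Section 8.0: medical conditions are screened by telephone at entry only.
- Section 3.0: the questionnaire outcomes are weight, height and psychosocial variables. The Revision History adds two instruments, the PAR and an exercise log, whose items are not shown.
- Section 18.0: "This study does not involve accessing medical records".
- Section 21.0: exercise takes place at home without staff present, so staff do not observe events.
- Section 17.0: there is no safety monitor or board.

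Nothing in the text shown supplies a route for medical events.

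**Contact spacing in the exercise arm**

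Inputs: weekly calls in month 1 and bi-weekly calls in months 2 and 3 (section 4.0); three sessions per week as the goal (section 4.0); 12 weeks (Study Summary). Each month is taken as 12 / 3 = 4 weeks.

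- Calls: 4 weekly + 8 / 2 = 4 bi-weekly = 8, which agrees with the eight telephone sessions in the Study Summary.
- Planned sessions in all: 12 × 3 = 36.
- Planned sessions in months 2 and 3: 8 × 3 = 24, and 24 / 36 = 67%.
- Planned sessions between calls in months 2 and 3: 2 weeks × 3 = 6. After an event at the first of these, 6 − 1 = 5 more are planned before the next call.

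These figures describe how far apart the prompts are. They are not probabilities of an event. They also show that a broader call question alone would often come too late to precede the next session, so the call-in instruction has to be widened as well.

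**The case against.** The strongest objection is that the finding depends on documents not shown. The intervention protocol holds the safety detail and may script a symptom question. The consent form, to which the Revision History says an instruction for injury was added, may tell participants to report other events. The 6- and 12-week questionnaires, the PAR and the exercise log may carry a health item, and section 3.0 is a list of endpoints rather than of questionnaire items. This stands as a condition on the conclusion. It does not remove the mismatch between sections 13.0 and 17.0: section 17.0 is where the protocol says how events come to light, and it does not refer to those documents.

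A second objection is that the text contains no contradiction, since section 17.0 sends all adverse events to the IRB and offers injury only as an example. That is correct about the scope of reporting. A broad duty to report does not tell the study that something has happened, and both prompts it states are narrow.

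A third is that the practical risk is small. This is a 50-person pilot labelled minimal risk, entry screening removes known heart disease and other unsafe conditions, the instructions to stop and seek help protect the participant whether or not the study hears of the event, and eight calls about exercise give room for it to come up. All of this stands and limits the urgency. Yet section 17.0 already chooses to ask about injuries proactively instead of waiting for them to be volunteered, and the same reasoning applies to the risk listed first.

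**Conclusion.** The concern holds. As written, injury has two stated detection routes and a medical event or change in medical status has none, although both trigger the same pause and the same IRB report. The fault lies in detection, not in the scope of reporting. It should be corrected, but it does not touch the primary endpoint or its analysis.

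The size can be given only as contact spacing: 14 days and 6 planned sessions between calls in months 2 and 3, a period holding 67% of planned sessions. The protocol gives no event rate, so the expected number of missed events cannot be estimated. The conclusion assumes that the supporting documents not shown (intervention protocol, consent form, questionnaire items and exercise log) do not already ask for medical events. Confidence is medium for that reason.

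**What to change.** In section 17.0, item 2, widen both the question asked on each call and the participant's instruction to contact the counselor, so that each covers, since the last contact:

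- any injury;
- any symptom that made the participant stop exercising or seek medical care;
- any new diagnosis, pregnancy or other change in medical status.

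State that a positive answer leads to the pause already set in section 13.0 and to the IRB report already required in section 17.0. The call-in instruction should ask for contact before the next exercise session, because it is the part that works between bi-weekly calls. If the intervention protocol already asks these things, say so in section 17.0 so that the two documents agree.

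The cost is one or two sentences in calls already planned. At no more than 1 minute per call, 25 participants × 8 calls = 200 minutes, about 3.3 hours. The 25 assumes 1:1 allocation of the 50 participants, since the ratio is not stated. If every wait-list participant later takes up the program, the upper bound is 50 × 8 = 400 minutes, about 6.7 hours. The downside is a few extra minor reports to log.
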